## Abstract

**Background:**

Chronic kidney disease (CKD) is an increasing epidemic globally that is associated with adverse health outcomes including end stage kidney disease (ESKD), cardiovascular disease (CVD), and death. American Indians (AIs) have a higher prevalence of CKD than most other racial/ethnic groups, due in part to a high prevalence of type 2 diabetes. Other genetic and environmental factors not yet identified may also contribute to the disproportionate burden of CKD in AIs.

**Method:**

We will establish 3 clinical centers to recruit AIs from the Southwest United States (US) to expand the Chronic Renal Insufficiency Cohort (CRIC) study. We will follow the current CRIC protocol for kidney and cardiovascular measures and outcomes, which include ambulatory monitoring of kidney function and the use of mobile health technologies for CVD sub-phenotyping, and compare the outcomes in AIs with those in other racial/ethnic groups in CRIC.

**Discussion:**

AI-CRIC will identify the role of various risk factors for rapid loss of kidney function among AIs of the Southwest US. In addition, to better understand the natural history of CKD and CVD in this high-risk population, we will identify unique risk factors for CKD and CVD progression in AIs. We will also compare event rates and risk factors for kidney and cardiovascular events in AIs with the other populations represented in CRIC.

## Background

Chronic kidney disease (CKD) is an increasing epidemic affecting people globally [1]. The prevalence of CKD among US adults is estimated at just under 15% [2], since American Indians (AIs) in the Southwest US have a prevalence of mild to moderate CKD of 17% [3]. Associated morbidity, mortality and economic burden mostly derive from progression to end stage kidney disease (ESKD) and cardiovascular disease (CVD). AIs suffer from substantial health disparities in the context of broad historical and contemporary social and economic inequality [3]. Risk factors for diabetic kidney disease, the predominant form of CKD among AIs, include the traditional factors such as hyperglycemia, hypertension, and inheritance, but may also include other factors such as exposure to various persistent environmental pollutants. In addition, the increasing prevalence of obesity in AI youth threatens to exacerbate the burden of CKD in these communities because the earlier onset of diabetes is associated with an increase in albuminuria, CKD, and ESKD in mid-life [4, 5]. Although the degree of proteinuria reduction from use of renin-angiotensin-aldosterone system inhibitors (RAASi) correlates with subsequent reduction in the rate of ESKD [6, 7], there are currently no markers available to predict the subsequent loss of kidney function in AI patients already treated with these agents. In addition to continuing the search for circulating and genetic markers of CKD progression, new paradigms have emerged to identify the role of subclinical risk factors (e.g., Cystatin C) for rapid loss of kidney function among AIs. Measurement of kidney function variability over time and detection of acute decrements in kidney function will be an important focus of the AI-CRIC Study. Several recent clinical trials examining treatments to slowing down CKD progression have failed to show outcome benefit in part because of the inability to identify prospectively, and randomize those at greatest risk of rapid progression while receiving standard of care treatment [8, 9].

CKD among AIs needs to be studied more deeply in order to answer many questions about the progression of CKD among AIs, as well as the prevalence of CVD in the setting of CKD in these populations. Assessment of morbidity and mortality associated with CKD, often from CVD, requires long-term study of affected individuals, and highlights the public health importance of this research initiative [10]. To address this burden of CKD in AI communities, our CRIC ancillary cohort study of 500 AIs (AI-CRIC) will improve our understanding of both potential risk factors for CKD progression, and the scope of this disease among AIs. Our study was designed to accomplish the following specific aims:

1) Identify unique risk factors for CKD and CVD progression and compare CKD and CVD event rates and risk factors between AIs and the other populations represented in CRIC.

2) Using an important paradigm shift for monitoring kidney function, we will conduct ambulatory monitoring of kidney function and damage using a handheld device analogous to a glucometer, and evaluate its relationship with exposure data.

3) Using mobile health technologies, we will conduct CVD sub-phenotyping and evaluate its relationship with exposures data.

Our study leverages the strengths of the current CRIC study and incorporates the planned activities of the next phase of the study by implementing contemporary CRIC protocols for kidney and cardiovascular measurements and outcomes in AIs.

## Methods/design

### Study overview

The overall goals of the proposed prospective cohort study are to: (a) precisely assess the extent to which the rates of CKD and CVD progression differ between AIs and other racial/ethnic groups based on standardized definitions used throughout CRIC; and, (b) to identify the association of CKD to the levels of potential environmental and occupational exposures unique to AIs residing in the American Southwest. To better understand the natural history of CKD/CVD in this high-risk population, we will implement the CRIC 2018 protocol of ambulatory monitoring of kidney function and damage along with evaluations of CVD sub-phenotypes using mobile health technologies. Data collection will take place at three sites located across the Southwest US. We will adopt the general methods and procedures of the parent CRIC protocol (http://www.cristudy.org).

We obtained Letters of Support from Zuni Comprehensive Community Health Center - Indian Health Services, First Nations Community Health Source, Pueblo of Zuni Tribal Governor, and NIDDK, NIH Phoenix.

### Inclusion and exclusion criteria

**Inclusion Criteria: Age:** Eligible age at enrollment is 21 to 80 years, which will ensure a sufficient number of CVD outcome events and statistical power while minimizing the impact of competing risks (deaths due to non-renal /non-CVD causes) and dropout. **Diabetes Status:** We will use the criteria of The Expert Committee on the Diagnosis and Classification of Diabetes Mellitus to diagnose diabetes status. **Glomerular Filtration Rate (GFR):** We will use the existing CKD-EPI equation to estimate GFR to assess eligibility [11]. Older participants will have lower levels of estimated GFR (eGFR) at enrollment. Many of the AIs speak their Native language along with English. Our community health representatives (CHRs) will help with study related procedures and will administer the consent in patients’ Native language such as Zuni or English depending on participant preferences.

**Exclusion Criteria at Enrollment:** [1] no consent [2]; life expectancy < 3 years [3]; institutionalized subjects [4]; ESKD or renal transplant [5]; renal cancer [6]; myeloma [7]; immunosuppression [8]; autosomal dominant polycystic kidney disease [9]; participation in any other Clinical trial [10]; current pregnancy; or, [11] current incarceration.

### Consent process

All sites participating in this study will use the same basic process to consent participants. The informed consent document will be structured such that it enables potential participants to indicate in which aspects of the study they are willing to engage (e.g., genetic component versus Biologic aspects). The consent process will cover all aspects of screening, baseline testing and subsequent follow-up visits. A separate section and signature page will be required for consent to collect a blood sample for genetic testing and storage of DNA.

Investigators, IRB-approved research coordinators, or CHRs will be responsible for obtaining consent. All personnel obtaining informed consent will have completed Collaborative Institutional Training Initiative (CITI) training, and received training from the principal investigator (PI) for consenting procedures in line with the UHM HSC Human Research Protections Office (HRPO) standard operating procedures (SOP) for Informed Consent titled, “SOP: Written Documentation of Consent (HRP-091)”. We will use a document of informed consent for this study. A copy of the signed/dated informed consent form will be given to every participant.

### Study timeline

Recruitment and patient enrollment will be completed in the first three [3] years of the study. Participant duration in the study may be as long as five years (60 months) if they are recruited in the first year of the study and complete all study visits. Some participants’ study duration will be shorter if they are recruited in Years 2 or 3 of the study.

### Study endpoints

The CRIC Study has a defined series of principal clinical outcome events that will be the focus of the primary longitudinal analyses. These outcomes can be broadly categorized as kidney disease events (ESKD or eGFR decline), cardiovascular events, patient-centered outcomes and death (see Table 1).

**Table 1 Tab1:** Non-kidney Clinical Outcomes

**Cardiovascular**	● Acute myocardial infarction ● Hospitalization for congestive heart failure ● Serious cardiac arrhythmia
**Peripheral Vascular**	● Amputation for peripheral artery disease ● Surgical or percutaneous revascularization for peripheral artery disease
**Cerebrovascular**	● Intraparenchymal hemorrhage ● Subarachnoid hemorrhage ● Large-vessel cerebral infarction ● Cardioembolic cerebral infarction ● Small-vessel cerebral infarction ● Cerebral infarction not otherwise specified
**Death**	● Atherosclerotic Coronary Heart Disease Death ● Cerebrovascular Death ● Other Atherosclerotic Disease Death ● Other Cardiovascular Disease Death ● Other Death ● Sudden Cardiac Death

### Research setting

#### Research locations

To enhance efficiency and ensure timely recruitment, we established a consortium experienced in conducting studies in AI communities. Participating organizations include the town of Guadalupe and NIDDK office in Phoenix; First Nation hospital and Albuquerque area Indian Health Services (IHS); and Zuni Pueblo, NM.

#### Recruitment methods

We will use the patient panel of CRIC investigators in our recruitment areas (Phoenix, AZ, Zuni, NM and Albuquerque, NM), since our sites have a track record for clinical studies recruitment. We will recruit participants from nephrology, diabetes, and internal medicine clinics. We will contact potential participants in compliance with HIPAA guidelines, guidelines of local IRBs, and the policies of each medical facility. We will approach potential participants either at the time of a visit, when they are referred through health care providers other than AI-CRIC investigators, or when they respond to advertising. We will provide a letter to potential participants that we screened through health care providers’ databases. The invitational letter will be signed by the local principal investigator and/or personal physician. We will also use community outreach, peer-to-peer recruitment, publish informational articles in local newspapers, and participate in local radio health-related broadcasting, to increase our sample size. Finally, the study staff will use mail, phone, or home visits for additional contacts.

We will then schedule those who are interested for a visit or phone call to assess eligibility. After initial screening, we will schedule those who are eligible and remain interested for an in-person screening and informed consent session. We will submit all recruitment materials for prior approval from the Human Research Review Committee (HRRC) of each site before we use them.

#### Community-based research staff

Our research staff will consist of four CHRs with associate degrees in nursing or health/life science. They will have responsibility for recruitment and performing the baseline and follow-up visits.

#### Study procedures

##### Initial pre-screening

AIs frequently live in homes not equipped with landlines, however majority of them carry mobile phones. CHRs will call prospective participants known to have phones based on our previous contacts through our continuous work in these communities. CHRs will also visit the homes and/or workplaces of potential participants. Potential participants may also be approached during scheduled visits to health professionals. If people are un-decided, CHRs will leave contact information and re-contact undecided participants in two weeks. If an eligible individual ultimately refuses participation, the CHR will document this on a refusal form.

##### Screening visit

Currently we have trained CHRs at all sites who will obtain the following: [1] informed consent [2]; demographic and contact information [3]; blood from a finger stick to measure A1C and Glucose using POC instruments [4]; urine to measure protein using a POC instrument; and [5] an eligibility questionnaire.

##### Baseline visit

The baseline study enrollment visit will occur within 45 days of the screening visit. We will follow the parent CRIC protocol [12] for all the methods and processes for the baseline visit including: [1] confirm eligibility [2]; medical history and physical examination [3]; approximately 65 cc of blood for fasting blood sample to measure glucose levels and glucose control, kidney function, cholesterol levels, electrolytes and measures of inflammation, and lymphocytes if consenting to DNA studies [5]; urine sample for protein, albumin, and urea nitrogen [6]; medication record [7]; ankle-brachial index [8]; anthropometrics [9]; questionnaires on dietary intake, physical activity, SF12, depression, cognitive function, and health resource utilization. This visit will last approximately 75 min.

##### Follow-up visits

We expect to follow participants from 30 to 54 months, depending on date of enrolment. We will repeat baseline measurements and observations annually. We will contact all participants six months after each of these visits to update contact information, ascertain interim outcome events, and assess health resource utilization. We will conduct follow-up visits at 11 to 13-month intervals.

##### Monthly finger-sticks

Patients will receive a handheld creatinine monitor (StatSensor Creatinine Monitor, about the size of a cell phone) and all the supplies needed to do finger-stick creatinine testing at home. Patients will be asked to do the testing at home monthly for one year and weekly for two months of that year. At the clinic visit, we will show patients a short video explaining how to do the testing. Afterwards, they will be asked to practice the test in the clinic before they leave to make sure they understand the process and to allow time for them to ask any questions. It will take about 15 min to learn how to perform finger-stick creatinine testing at home. For each test, the patient will first do a “finger-stick” to get a drop of blood from the tip of their finger. They will place the drop of blood on the edge of the testing strip and insert the strip into the meter. The meter will display the creatinine measurement. Once they have measured their creatinine, they will be asked to report the value by calling the AI-CRIC Study. They will discard the test strip after completing the test.

##### Monthly urine albumin testing

patients will receive urine diagnostic dipsticks and scan cards (Scanwell Health Urine Dipsticks and Scan Cards) and will be asked to download the “CRIC at Home” smartphone application. They will be asked to do the testing at home monthly for one year and weekly for two months of that year on the same day they perform the finger-stick creatinine test. At their clinic visit, we will describe the process to them. Patients will be asked to practice the test in the clinic before they leave to make sure they understand the process and to allow time for them to ask any questions. It will take about 15 min to learn how to perform the urine albumin testing at home.

Before performing the urine test, patients will be asked to complete a brief survey on risk factors for sudden changes in kidney function through the “CRIC at Home” smartphone application. For each test, they will first collect a urine sample in a specimen cup. After collecting the urine, patients will dip the urine diagnostic dipstick in the urine and then place on the diagnostic scan card and wait for the colors to develop. Using their smartphone, they will launch the “CRIC at Home” application and it will guide them through the process of taking a picture of the diagnostic scan card. After the application finishes scanning the picture, the test result will be displayed. The image and result are stored on the application. This application is unencrypted; however, only the patient’s result and unique ID are stored on the application and all study information will be removed after completion of the study. Once the patient has tested their urine, they will be asked to report the value by calling the AI-CRIC Study. Patients will discard the dipstick and scan card after completing the test.

We will give a printed schedule to patients at the clinic visit to remind patients when to perform the finger-stick creatinine and urine albumin tests. We may also call patients by telephone or contact them by email to remind them to perform these tests and let us know their results. A short questionnaire will also be given to patients to provide feedback on their experience with these home tests, which can be mailed back to us in a pre-paid envelope.

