##### Analytical plan for second aim

To characterize potential non-linear patterns of CKD progression, we will implement analyses previously described by Li et al. [13] Briefly, we will initially apply a Bayesian smoothing technique to estimate each patient’s eGFR or proteinuria trajectory as a smooth curve. As such, its slope can be calculated month by month, accommodating a possible change in rate of progression over time [13]. We will then classify patients based on disease trajectory using iterative measures. This can be accomplished using two approaches. First, we plan to use latent class mixed effects models [14, 15] as described above. Second, the Bayesian smoothing technique [13] will allow us to estimate the “most likely” trajectory by the average of the generated Monte Carlo curves and the observed variation in curves around the mean estimated curve.

To quantify intra-individual variability in kidney function or damage, we propose to initially follow the approach previously taken by Al-Aly and colleagues [16]. We will define within-person variability as the coefficient of variation of a regression line fitted to all of the monthly fingerstick creatinine-based eGFR or bimonthly protein measures for each individual participant. The general concept of this approach is to calculate the deviation of the measured creatinine-based eGFR, for example, from its fitted value based on a linear regression model for each participant. This measure of kidney function variability has an advantage because it is normalized to the average value for each individual, which means it is a dimensionless metric that can be readily compared across participants who have different absolute levels of eGFR [16]. Furthermore, to improve the precision of the estimation of the intra-individual variability in kidney function or damage, we can take advantage of using the previously identified non-linear values while calculating variability. Depending on the question of interest, and the focus on either pathophysiology or prediction of disease, we will use logistic, failure-time, repeated measure or predictive analyses as described above. These measures of kidney function or damage will be defined over the course of 1 year for individuals, so the outcome assessment period in these models will begin at the end of the sub-protocol period or AKI episode.

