Despite the strengths of the study, there are some potential pitfalls and limitations; we recognize that observed monthly changes in eGFR based on fingerstick creatinine measures may not reflect actual changes in underlying kidney function but rather variability in creatinine production. Our plan is to characterize potential non-linear eGFR trajectories over a 12 month testing period. With regards to urine albumin/protein excretion testing using the proposed urine diagnostic testing methods, there are well-known challenges in standardizing and accurately quantifying the amount of albumin or total protein by these methods. Nonetheless, the ability to detect the presence of and changes in semi-quantitative measures of urine albumin or protein has important potential clinical and prognostic implications. Furthermore, despite any measurement limitations, our study will provide key insights into the potential bimonthly variability in semi-quantitative urine albumin/protein excretion within the context of concurrent measures of eGFR. The total period of time during which each participant will wear the monitors is limited by features of the devices used (data storage capacity of the Zephyr BioPatch, and battery life in the ZIO XT Patch). While both devices will be worn long enough to capture diurnal variations, it is possible that some participants will wear the devices during periods in which the type and level of their activities are nonrepresentative. Finally, a larger number of patients may drop out from the study than we considered in the power calculations. The drop-out rate will be monitored and the enrollment target may be adjusted upwards.

In conclusion AI-CRIC study will help us to learn more about ESKD and its progression and relationship with CVD.

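### The home urine test fixes the day but not the void and states no concentration correction, yet its variability is interpreted as variability in excretion

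*Protocol article*

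**What the plan says.** All references are to the Protocol article.

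- **Home test** (Monthly urine albumin testing). The device is described thus: "patients will receive urine diagnostic dipsticks and scan cards (Scanwell Health Urine Dipsticks and Scan Cards". Tests are done "monthly for one year and weekly for two months of that year on the same day they perform the finger-stick creatinine test". The steps run from a short survey, through dipping, scanning and telephoning the value, to discarding the strip. The only instruction on the specimen is "For each test, they will first collect a urine sample in a specimen cup". No void is specified. The section does not say whether the strip reports a concentration or a creatinine-corrected ratio.
- **Analysis** (Analytical plan for second aim). The plan will "estimate each patient’s eGFR or proteinuria trajectory as a smooth curve" and classify patients by trajectory. It also defines within-person variability as a CV about each person's own regression line, applied to the fingerstick eGFR or to the protein measures. The plan counts it an advantage that this CV is scaled to each person's average.
- **Interpretation** (Discussion). The article expects that "our study will provide key insights into the potential bimonthly variability in semi-quantitative urine albumin/protein excretion". It concedes in general terms that these methods are hard to standardise and quantify. It does not mention urine concentration.
- **Clinic urine** (Screening visit and Baseline visit). Screening lists "urine to measure protein using a POC instrument". Baseline, repeated annually, lists "urine sample for protein, albumin, and urea nitrogen", under the statement "We will follow the parent CRIC protocol [12] for all the methods and processes for the baseline visit". UACR appears in the abbreviation list.

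**The concern.** A plain dipstick in a spot sample reads concentration, that is, excretion divided by urine flow. A participant whose excretion is steady but who tests a concentrated sample one month and a dilute one the next will appear to have variable kidney damage. The stated interpretation therefore does not follow from the stated procedure.

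The trajectory classes and variability scores are meant to be related to later outcomes. Unrelated dilution noise would weaken a real association. If fluid intake, diuretic use or concentrating ability differ by risk, dilution could also contribute an association of its own. A home reading cannot be corrected afterwards if neither the void nor a urine creatinine was recorded.

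For the fingerstick, the Discussion does name a source of variation other than kidney function, namely creatinine production. It names no counterpart for urine.

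**Working it through.** **1. The plan's only second-aim figure.** Inputs from the second-aim power section: difference 5.0, SD 9.05, 75 per group, two-sided 0.05.

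- Noncentrality = 5.0 / (9.05 × √(2/75)) = 3.38.
- Power = 92.3% (normal) or 91.9% (t, 148 df), against the stated figure of more than 90%.

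It reproduces. It concerns one-year eGFR change and does not depend on the urine readings.

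**2. Share of within-person variance due to dilution.** Write log concentration = log excretion − log urine flow, with the two parts independent and lognormal. Let CVe be the within-person CV of excretion and CVd that of dilution. Then

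share = ln(1 + CVd²) / [ln(1 + CVd²) + ln(1 + CVe²)].

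The documents give neither CV, so both are assumed to lie between 0.2 and 0.8.

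| CVe | CVd | Calculation | Dilution share |
|---|---|---|---|
| 0.8 | 0.2 | 0.039 / (0.039 + 0.495) | 7% |
| 0.5 | 0.3 | 0.086 / (0.086 + 0.223) | 28% |
| equal | equal | – | 50% |
| 0.3 | 0.5 | 0.223 / (0.223 + 0.086) | 72% |
| 0.2 | 0.8 | 0.495 / (0.495 + 0.039) | 93% |

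**3. Does scaling to the person's mean help?** Simulation of the plan's metric: residual SD about a fitted line divided by the person's mean, 12 monthly readings treated as continuous, CVe fixed at 0.30.

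| CVd | Mean residual CV |
|---|---|
| 0 | 0.29 |
| 0.3 | 0.41 |
| 0.5 | 0.55 |

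The scaling removes differences in level between people. It leaves dilution that changes from void to void within a person.

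**4. How well does the metric rank people?** Same metric, with CVe assumed to vary between people from 0.1 to 0.6. The table gives the squared correlation of the score with true CVe.

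| CVd | Squared correlation |
|---|---|
| 0 | 0.67 |
| 0.25 | 0.44 |
| 0.35 | 0.31 |
| 0.50 | 0.17 |
| 0.60 | 0.11 |

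A rerun with a different random seed agreed to within 0.01.

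**5. Category changes when excretion is perfectly constant.** Assumptions: 19 readings (10 monthly plus about 9 weekly), cut points at 10, 30, 100 and 300 mg/dL, and person means spread evenly on the log scale.

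| Range of person means (mg/dL) | CVd | Consecutive readings in different categories | People spanning two or more category steps |
|---|---|---|---|
| 10–300 | 0.25 / 0.35 | 25% / 34% | 1% / 15% |
| 10–300 | 0.50 / 0.60 | 45% / 50% | 51% / 71% |
| 1–1000 | 0.50 / 0.60 | 30% / 34% | 26% / 38% |

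These figures depend heavily on where person means lie relative to the cut points. They illustrate the mechanism and do not estimate its size.

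**The case against.** **Silence in a condensed article.** The strip is commercial and might carry a creatinine pad. The app and the printed schedule are not shown, and the void could be specified there. This stands in part, which is why the point is conditional on what the strip reports. But the section describes the participant's steps down to discarding the strip and fixes the day, and the excretion interpretation is an affirmative statement rather than an omission.

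**The limitation is already conceded.** The Discussion calls the readings semi-quantitative and admits problems of standardisation. That is fair, but it neither names dilution nor acts on it.

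**A reader might infer that the clinic samples lack urine creatinine, so that no albumin-to-creatinine ratio can be formed.** The documents do not support this. The baseline list omits urine creatinine, but the visit follows a parent protocol that is not shown, and UACR is among the abbreviations. The clinic samples are also annual and are not the home series behind the variability score.

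**A reader might also infer that the urine score mostly measures dilution.** That is not established either. A range of 7% to 93% does not settle which component dominates. The category simulation sets true variability to zero, so it cannot give a share.

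**First-morning sampling is not a complete cure.** If it lowers the dilution CV to 0.25–0.35 (assumed), 25% to 34% of consecutive readings still change category in step 5. This stands; the remedy reduces the noise without removing it.

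**Conclusion.** The point holds for the home test. As written, the procedure leaves the void open and states no concentration correction, while the result is labelled excretion. Unless the strip reports a creatinine-corrected ratio, independent void-to-void dilution inflates the within-person CV, and scaling to the person's mean does not prevent it.

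The size cannot be settled from the documents. Dilution accounts for 7% to 93% of within-person log variance over assumed CVs of 0.2 to 0.8. The squared correlation of the score with true variability falls from 0.67 to between 0.44 and 0.11 at assumed dilution CVs of 0.25 to 0.60. These results rest on independent lognormal components and, for the score, on continuous readings. No sample size or power figure changes.

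The change is worth making before home testing starts, because it is cheap then and cannot be made afterwards. Confidence is medium, since it depends on what the strip reports.

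**What to change.** 1. In Monthly urine albumin testing and on the printed home schedule, require the first-morning void for every home urine test.
2. State what the strip reports. If it gives an albumin-to-creatinine ratio, analyse that ratio. If not, describe the urine measure in the Analytical plan for second aim and in the Discussion as variability in urine albumin/protein concentration, not excretion.
3. Confirm that an annual clinic UACR is available under the parent protocol, and use it as the reference for the home readings.

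Cost: one line on a schedule that already exists, some wording, and one confirmation. Testing at a set time may lower adherence slightly. The fingerstick is done on the same day and need not move.
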